### Control group

#### Group 3 – service as usual

Participants allocated to the control group will receive “service as usual” only. This consists of participants continuing to receive OPUS or community mental health treatment. Also, it involves individual case management and medical review, referral to external vocational agencies, and involvement in group programs which may involve participation in vocationally oriented groups. The psychiatric treatment provided will be the same in all three groups throughout the trial period with the one exception that controls do not get the integrated IPS intervention. In general, the participants allocated to the control group are to have close mandatory contact with the local vocational authority (job centers), depending on what kind of benefits they receive. Hence, the participants in the control group will receive a variety of vocational rehabilitation support at the job centers in accordance with the train and place principle.

### Blinding

Owing to the nature of the intervention, neither participants nor staff can be blinded to allocation but are instructed not to reveal details that may cause the research assistant to deduce which intervention the participants are receiving. The research assistants who perform the assessments at baseline and follow-up will be blind to allocation. If the blinding cannot be maintained, a research assistant from the other site will perform the follow-up interviews. Blinding will be maintained until the end of the trial. Statistical analyses will be conducted with intervention groups coded as, for example, X, Y, and Z. Conclusions will be drawn with the blinding intact. First, we will assume that X is experimental group 1, Y is experimental group 2, and Z is control group 3. Then we will draw five additional conclusions, assuming the remaining five combinations. After this, the blind will be broken.

### Outcome and assessments

The primary outcome is “hours in competitive employment or education” measured from baseline to 18-month follow-up. Employment and enrollment in education will be identified by using register data. Hours in competitive employment will be extracted from an extended version of the Danish Register for Evaluation of Marginalization (DREAM) database administered by the National Labor Market Authority [30]. The DREAM database contains information on employment, sickness leave, and education eligible for state education grants, disability pension, social security, and sickness benefits. The register covers the entire population, and data can be linked to a range of different registers, including the Danish income register, making it possible to obtain the exact number of employment hours. Data on education will be extracted from education statistics hosted by Statistics Denmark (http://www.statbank.dk) and supplemented by data from interviews for more detailed information on part-time studies.

The primary outcome will be supported by several other secondary and explorative outcome measures. Secondary outcomes are work or education at some point during the follow-up period (yes/no), days to first employment or beginning of education, cognitive impairment, functional level, self-esteem, and self-efficacy assessed at baseline and 18-month follow-up. Data on employment and education will similarly be extracted from registers. Furthermore, semi-structured interviews using the Personal and Social Performance (PSP) scale [31] and the Brief Assessment of Cognition in Schizophrenia [32] will be used to assess cognitive impairment and functioning. Standardized validated survey instruments, including the Rosenberg self-esteem scale [33] and the General Self-Efficacy scale [34], will be used to assess self-esteem and self-efficacy. All secondary outcomes and the assessment instruments used are outlined in Table 2.

**Table 2 Tab2:** Primary and secondary outcomes and data collection

Outcomes	Source of collection	Assessment	Baseline	18-month follow-up
Primary outcome	Register-based/Interview	Hours in competitive employment or education in follow-up period		X
Secondary outcomes	Register-based	Competitive employment or education at some point during follow-up period		X
	Register-based	Days to first employment or beginning of education		X
	Obtained through interview	Cognitive function measured with the Brief Assessment of Cognition in Schizophrenia [32] (BACS)	X	X
	Obtained through interview	Function measured with Personal and Social Performance (PSP) Scale [31]	X	X
	Self-reported questionnaire	Self-efficacy measured with General Self-Efficacy (GSE) scale [37]	X	X
	Self-reported questionnaire	Self-esteem measured with the Rosenberg Self-Esteem scale [38]	X	X

To avoid the risk of multiplicity and type I errors, we will limit our secondary outcomes to outcomes with at least 80 % power. Other outcomes are considered “exploratory” when drawing conclusions. This means that we will consider any statistically significant result in any of these outcomes as exploratory or hypothesis-generating. This is because we have no sample size estimation for these outcomes, and thus the risk of an early false positive is increased; it is further increased because of the risk of multiplicity as a result of too many outcomes.

Exploratory outcomes cover the 30 and 60 months of register follow-up along with additional vocational measures that will provide a more nuanced picture of vocational status, including average monthly earnings and hours of work per week among those who obtain competitive employment. Furthermore, a range of non-vocational outcomes such as client satisfaction, health-related quality of life, empowerment, recovery, and substance abuse will be used to address other important factors hypothesized to influence the participants. Psychopathology will be measured to ensure no adverse effects of the intervention.

All exploratory and safety measures and the assessment instruments used are outlined in Tables 3 and 4. Trained and certified research assistants will perform all assessments. Inter-rater reliability tests will be performed prior to the trial and at least quarterly throughout the assessment period on the following instruments: Scale for the Assessment of Negative Symptoms [35], Scale for the Assessment of Positive Symptoms [35], PSP scale [31], and Hamilton Depression Scale (HAM-D6) [36]. The aim is to achieve an interclass correlation coefficient of more than 0.7. Consensus ratings will be performed on the remaining instruments.

**Table 3 Tab3:** Explorative measures and data collection

Outcomes	Source of collection	Assessment	Baseline	18-month follow-up	30 + 60-month register follow-up
Explorative outcomes	Register-based	Hours in competitive employment or education in follow-up period			X
	Register-based	Competitive employment or education at some point during follow-up period			X
	Register-based	Days to first employment or beginning of education			X
	Register-based	Days in employment or education		X	X
	Register-based	Average monthly earnings		X	X
	Register-based	Hours of work per week among those who obtain competitive employment		X	X
	Register-based	Long-term sick leave		X	X
	Register-based	Social benefits	X	X	X
	Obtained through interview	Function measured with Global Assessment of Functioning (GAF) [39]	X	X	
	Obtained through interview	Health-related quality of life measured with 12-Item Short Form Health Survey (SF-12) [40]	X	X	
	Self-reported questionnaire	Recovery measured with Mental Health and Recovery Measure (MHRM) [41]		X	
	Self-reported questionnaire	Empowerment measured with Empowerment Scale [42]	X	X	
	Self-reported questionnaires	Satisfaction with treatment. Measured with Client Satisfaction Questionnaire (CSQ) [43]		X	
	Register-based	Use of mental health services	X	X	X
	Obtained through interview	Substance abuse measured with Alcohol Use Disorders Identification Test (AUDIT) [44]	X	X	
	Self-reported questionnaire	Health-related quality-of-life measured with EQ 5D(EuroQOL five dimensions questionnaire) [45]	X	X

**Table 4 Tab4:** Safety measures and data collection

Outcome measure	Source of collection	Assessment	Baseline	18-month follow-up	30 + 60-month register follow-up
Safety measures	Obtained through interview	Psychotic and negative symptoms measured with Scale for the Assessment of Positive Symptoms (SAPS) and Scale for the Assessment of Negative Symptoms (SANS)	X	X	
	Obtained through interview	Depressive symptoms measured with Hamilton Depression Scale [36] (HAM-D6)	X	X	
	Obtained through interview	Suicidal ideation and actions. Measured with European Parasuicide Study Interview Schedule (EPSIS)	X	X	
	Death cause register, Civil Registration System (CPR)	Deaths (all causes)	X	X	X
	Hospital records	Number and length of hospital admissions both somatic and psychiatric		X	X
	Hospital records	Use of outpatient services	X	X	X

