### Sample size and power calculation

No previous IPS trials or similar studies have been conducted in Denmark that could contribute to an estimation of the expected average number of hours of work among participants in the IPS intervention. A European IPS multicenter trial found a difference between the IPS group and the control group (vocational services) of 150 h in competitive employment in an 18-month follow-up period, and standard deviation was 500 [19]. A difference of 150 h in competitive employment or education is considered clinically relevant. If the outcome within each intervention group is normally distributed with a standard deviation on 500 and with a true mean difference of 150 between the intervention and the control group, the present trial will need 250 participants in both intervention arms and additionally 250 control participants to be able to reject the null hypothesis that the population means of the experimental and control groups are equal with probability (power) of 80 %. The type I error probability associated with the null hypothesis is 1.25 %. A type I error of 1.25 % was chosen to give the possibility to make four comparisons: (1) IPS versus service as usual, (2) IPS versus IPS enhanced, (3) IPS enhanced versus service as usual, and (4) IPS + IPS enhanced versus service as usual. If we encounter difficulties in recruiting 250 participants to each group, we will exclude comparison (4) as a primary comparison. With three primary comparisons, we use a type I error of 1.67 % in the sample size calculation, accumulating a sample size of 236 patients in each group. Power calculations on calculations of the secondary outcome measures were carried out (Table 5) and indicate that a sample size of 250 patients per group would be adequate to detect relevant significant differences.

**Table 5 Tab5:** Power calculation

Outcome measure	δ expected difference in mean	σ expected standard deviation	α	Power	Reference
Days to first employment or beginning of education	68	45	0.0125	1.000 (*t* test)	Bond et al. [8] (2008),
Cognitive function	0.3	0.7	0.0125	0.989 (*t* test)	McGurk et al. [13] (2005)
The Brief Assessment of Cognition in Schizophrenia [32]					
Function measured with Personal and Social Performance (PSP) scale [31]	7	14	0.0125	0.999 (*t* test)	Kawata et al. [31] (2008). Nasrallah et al. [46] (2008) (No IPS studies use PSP scale. δ is estimated)

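### Keeping only secondary outcomes with 80 % power does not limit type I error: six remain, the 1.25 % level covers comparisons within one outcome only, and the stated caution leaves them out

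*Protocol article*

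**What the plan says.** Outcome and assessments gives the rule and its purpose together: "To avoid the risk of multiplicity and type I errors, we will limit our secondary outcomes to outcomes with at least" 80 % power. All other outcomes are classed as exploratory, and a significant result on them counts as hypothesis-generating only. The reason given is "because we have no sample size estimation for these outcomes, and thus the risk of an early false positive is increased". The paragraph adds the large number of outcomes as a further source of risk.

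Six secondary outcomes pass the filter: "Secondary outcomes are work or education at some point during the follow-up period (yes/no), days to first employment or beginning of education, cognitive impairment", then "functional level, self-esteem, and self-efficacy assessed at baseline and 18-month follow-up".

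Sample size and power calculation sets the test level for the primary outcome at 1.25 %, which "was chosen to give the possibility to make four comparisons": IPS against usual service, IPS against enhanced IPS, enhanced IPS against usual service, and both IPS arms together against usual service. Table 5 uses alpha 0.0125 for each of the six secondary outcomes, with stated powers from 0.807 to 1.000. The article states no adjustment across the six.

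**The concern.** The rule is offered as protection against type I error, but it selects outcomes on a quantity that has no bearing on type I error. Power is the chance of a significant result when a given effect exists. The false-positive rate is the chance of one when no effect exists, and the test level fixes it. An outcome with 99 % power and one with 30 % power, both tested at 0.0125, have the same false-positive rate. Whether anyone calculated a sample size for an outcome makes no difference either.

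What is at stake is how a significant secondary result may be read. The article tells readers that the risk has been dealt with for secondary outcomes and keeps its caution for the others. If hours in employment or education show no difference, a chance result on cognition, functioning, self-esteem or self-efficacy could be reported without the caution that the same result would carry in the exploratory tier.

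**Working it through.** **Inputs from the article.** Three equal groups of 250; alpha 0.0125 per comparison; four comparisons; six secondary outcomes; primary difference 150 h, SD 500, power 80 %. **Assumptions.** Two-sided tests (sidedness is not stated), all null hypotheses true, all four comparisons made for each secondary outcome, and a common correlation between outcomes, which is varied.

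**1. Reproduce the plan's own figures.** n per group = 2(z₁₋α/₂ + z₁₋β)²(SD/difference)² = 2 × (2.498 + 0.842)² × (500/150)² ≈ 248. The article states 250, and a t test with 250 per group has power 0.801. A one-sided test would need only 212, so the two-sided reading fits. The same level with 250 per group reproduces the Table 5 powers for days to first employment (1.000), cognition (0.989), PSP (0.999) and self-efficacy (0.880). The self-esteem and yes/no employment rows do not reproduce exactly from the printed inputs (0.9998 against 0.992, and 0.873 against 0.807). Both stay above 80 %, so this point is unaffected.

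**2. Compare power with alpha.** In Table 5 power runs from 0.807 to 1.000 while alpha stays at 0.0125. The table itself shows that the two are set separately.

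**3. Error within one outcome.** The four contrasts are correlated because they share groups. Pairwise contrasts correlate at 0.5 in absolute value. The pooled contrast (½, ½, −1) and IPS against usual service (1, 0, −1) correlate at 1.5/(√1.5 × √2) = 0.87. Simulation with this structure gives 3.6 % for at least one false positive among the four, below the Bonferroni bound of 4 × 1.25 % = 5 %. So 1.25 % does its work within one outcome.

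**4. Error across six outcomes.** If the outcomes are independent: 1 − (1 − 0.036)⁶ ≈ 19.8 %. With correlated outcomes, by simulation:

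| Correlation between outcomes (assumed) | At least one false positive |
|---|---|
| 0 | 19.8 % |
| 0.3 | 18 % |
| 0.5 | 16 % |
| 0.7 | 13 % |
| 0.9 | 8.4 % |

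Any employment or education and days to first employment or education describe the same register event. With 0.8 to 0.9 for that pair, 0.5 among the four clinical scales and 0.1 to 0.3 across, the result is about 16 to 17 %.

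**5. Outer limits.** The Bonferroni bound is 6 × 4 × 0.0125 = 30 %, and treating all 24 tests as independent gives 1 − 0.9875²⁴ = 26.1 %. Both ignore the shared groups and overstate the risk. If only one comparison were made per secondary outcome, six independent tests would give 1 − 0.9875⁶ = 7.3 %. Under the article's fallback of three comparisons at 1.67 %, the figure is 23.8 % with independent outcomes and 19 % at correlation 0.5.

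**The case against.** **The filter is not without effect.** It leaves six secondary outcomes and places the rows of Table 3 in a pre-declared exploratory tier. Fewer tested outcomes mean fewer chances of a false positive, and the article itself names too many outcomes as a risk. This stands: it would be wrong to say that the rule does nothing. But any rule that cut the list to six would do the same, and being adequately powered adds nothing to it.

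**Low power does matter for credibility.** When power is low, a larger share of significant results is false. That is true, but it is a different quantity. The article speaks of type I errors, and that rate does not change with power.

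**A reader might infer that secondary results are to be declared confirmatory.** The article does not say so. It describes secondary and exploratory measures alike as supporting the primary outcome. What can be said is narrower: the hypothesis-generating label is attached to the other outcomes only, so by contrast secondary results escape it.

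**A reader might infer that the missing adjustment across outcomes is itself the error.** It is not. Such an adjustment is commonly left to the analysis plan, which is not shown, and whether secondary outcomes need familywise control is partly a matter of choice. The point rests on the protection that the article claims. That claim would need correcting even if an adjustment exists elsewhere.

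**A reader might quote a flat 20 %.** That is the independence case, which cannot hold exactly, since two of the six outcomes describe the same event. The use of four comparisons per secondary outcome is also inferred, from the alpha column of Table 5; the text attaches them to the primary calculation.

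**The power statement is not at fault here.** The sentence that the Table 5 calculations "indicate that a sample size of 250 patients per group would be adequate to detect relevant significant differences" concerns power only and makes no claim about type I error.

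**Conclusion.** The point holds as a wrong stated rule. A power threshold does not avoid type I error, and the absence of a sample size estimate does not raise it. The 1.25 % level holds the error to about 3.6 % within one outcome but does not extend over six. If every null hypothesis is true and all four comparisons are made for each outcome, the chance of at least one significant secondary result is about 13 to 20 % for assumed correlations from 0.7 down to 0. It remains above 5 % even at 0.9. The exact figure depends on correlations that the article does not give.

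The consequence is limited to the reading of secondary results. The primary comparisons, their level and the sample size are untouched. The correction is still worth making, because it changes what the trial may conclude from a significant secondary result, especially after a null primary result.

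**What to change.** In Outcome and assessments:

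- Delete the statement that a limit of 80 % power avoids multiplicity and type I error. The power criterion can stay if its purpose is given correctly: to choose outcomes on which the trial can be informative, and to keep the list short.
- Delete the statement that lack of a sample size estimate increases the false-positive risk. The number of outcomes is reason enough for the exploratory label.
- State that the 1.25 % level controls error over the group comparisons within one outcome, not across outcomes.
- Extend the existing caution: significant secondary results are supportive or hypothesis-generating, reported with confidence intervals, unless control across the six outcomes is prespecified.

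If the investigators want to claim secondary effects as established, one option is to test the secondary outcomes for a comparison only when the primary outcome is significant for that comparison, and then apply Holm's procedure across the six. This is a choice, not a requirement, and it must be fixed before the groups are compared. If the analysis plan already contains such a rule, a reference to it is enough.

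The cost is a few sentences of text, and fewer secondary results can be claimed as established effects. Data collection, sample size and the primary analysis do not change.

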**Methods/Design:**

The trial design is an investigator-initiated, randomized, assessor-blinded, multi-center trial. A total of 750 patients with severe mental illness will be randomly assigned into three groups: (1) IPS, (2) IPS enhanced with cognitive remediation and work-related social skills training, and (3) service as usual. The primary outcome is number of hours in competitive employment or education at 18-month follow-up. Secondary and exploratory outcomes are money earned, days to first employment, symptoms, functional level, self-esteem, and self-efficacy at 18-month follow-up. Thirty- and 60-month follow-ups will be register-based.

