### Data analysis plan

The main null hypothesis to be tested is that there is no difference between the three groups in hours in competitive employment or education in the 18-month follow-up period. All randomized participants will be analyzed, including those who stop receiving treatment, according to the intention-to-treat principle. All continuous outcome measures, including the primary outcome “hours in competitive employment or education”, will be analyzed by using generalized linear models. In situations in which the continuous measure is non-normally distributed, a non-parametric model will be used. Multiple imputations will be used to impute a distribution of missing values. Furthermore, linear mixed models with repeated measurements and unstructured covariance matrixes will be used to assess the potential interaction between time and intervention. The dichotomous secondary outcome “work or education at some point during the follow-up period” will be analyzed by using logistic regression. The secondary outcome “time-to-employment or education” will be analyzed by using the Cox proportional hazards model. All models will be adjusted for the stratification variables.

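### Table 4 schedules no baseline for hospital admissions, the only safety row without one, so the admissions comparison is valid but less precise than obtainable data would allow

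*Protocol article*

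**What the plan says.** Table 4, in the section Outcome and assessments, has six safety rows. Five are ticked at baseline: psychotic and negative symptoms, depressive symptoms, suicidal ideation and actions, deaths, and outpatient use. The sixth, "Number and length of hospital admissions both somatic and psychiatric", is ticked at 18 months and at 30 and 60 months only.

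The next row, "Use of outpatient services", has the same stated source, hospital records, and is ticked at every time point including baseline. In Table 3 the exploratory item "Use of mental health services" is register-based and also has a baseline tick. The deaths row of Table 4, sourced from "Death cause register, Civil Registration System (CPR)", is ticked at baseline as well.

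The last column of Table 4 is headed "30 + 60-month register follow-up", and the abstract says "Thirty- and 60-month follow-ups will be register-based". Both hospital-records rows are ticked in that column.

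On adjustment, the Data analysis plan says "All models will be adjusted for the stratification variables". According to the section Randomization these variables are sex, work history, work readiness and site. The section Ethical considerations gives hospitalization as one example of the adverse events to be registered and reported.

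**The concern.** A baseline value of a safety measure describes the arms before treatment and can serve as a covariate. For hospital use, the pre-trial value is a plausible predictor of the later one. The table provides it for outpatient use but not for admissions, and admissions bear on an adverse event that the article names. The one baseline tick that cannot mean anything, for deaths among people who have just consented and been assessed, stands in the row directly above the one left blank.

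What is at stake is the width of the confidence interval for admissions. A harm comparison with a wider interval than necessary is less able either to reveal an increase in admissions or to rule one out.

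A smaller point is the source. Two rows are attributed to hospital records but ticked under a column headed as register follow-up, so the reader cannot tell what is extracted at 30 and 60 months.

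**Working it through.** The article attaches no event rate, power or standard deviation to admissions, so there is no figure of its own to reproduce. The check has three steps.

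**1. The rows side by side**

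| Row | Table | Stated source | Baseline | 18 months | 30 + 60 months |
|---|---|---|---|---|---|
| Deaths | 4 | Registers | ticked | ticked | ticked |
| Admissions | 4 | Hospital records | blank | ticked | ticked |
| Outpatient use | 4 | Hospital records | ticked | ticked | ticked |
| Mental health service use | 3 | Register-based | ticked | ticked | ticked |

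The cells line up consistently across these rows, so they are taken as printed. Pre-trial hospital use is evidently obtainable: the same source supplies it for outpatient contacts. A baseline for deaths can hold no information, because every participant is alive at consent.

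**2. Adjustment**

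None of the four stratification variables measures earlier hospital use. They cannot be expected to stand in for prior admissions.

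**3. What the covariate could be worth**

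Let r be the correlation between pre-trial and follow-up admissions, after allowing for the stratification variables. The article does not give it. Values of 0.3 to 0.5 are assumed for illustration. Under a linear model with randomised arms:

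- Variance of the adjusted contrast, relative to the unadjusted one: 1 − r²
- Equivalent increase in sample size: 1/(1 − r²)
- Relative standard error: √(1 − r²)

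| Assumed r | 1 − r² | Variance removed | 1/(1 − r²) | √(1 − r²) |
|---|---|---|---|---|
| 0.3 | 1 − 0.09 = 0.91 | 9 % | 1.10 | 0.95 |
| 0.5 | 1 − 0.25 = 0.75 | 25 % | 1.33 | 0.87 |

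At the planned 250 per arm, an adjusted analysis would have about the precision of an unadjusted one with 250/0.91 = 275 to 250/0.75 = 333 per arm. The confidence interval would be about 5 % to 13 % narrower.

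These figures are only a guide. Numbers of admissions and bed-days are usually skewed with many zeros, and the linear result does not carry over exactly to count or non-parametric models.

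**The case against.** The strongest reply is that this is a clerical slip with little behind it. A blank cell in a data-collection table is not an analysis decision. The Data analysis plan names no baseline value as a covariate for any outcome, ticked or not, and it does not say that the stratification variables are the only covariates. Covariates for a safety outcome are commonly left to a statistical analysis plan, which is not shown here. The Table 3 item on mental health service use has a baseline tick and might include psychiatric admissions; the article does not define it.

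Much of this stands. A reader might infer that the analysis will ignore pre-trial admissions. The article supports less than that: the schedule as printed does not provide them. Even so, a schedule without the data fails to support an analysis that would use them. The Table 3 item, if it does include admissions, could not cover the somatic ones that Table 4 also counts.

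Four stronger readings are also not supported:

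- **That the safety comparison is biased.** Allocation is central, concealed and stratified, so the unadjusted contrast is unbiased. Chance imbalance in prior admissions is already reflected in its standard error.
- **That admissions are the main safety outcome.** The article ranks no safety measure first. It names psychopathology as the check for adverse effects, and deaths are at least as objective.
- **That admissions will be missed when participants move.** The article does not say that hospital records means the files of particular hospitals. The different source in Table 3 belongs to a different measure and is not in itself a contradiction.
- **That the ticks for deaths and admissions were swapped.** This is possible, but the deaths tick may simply be superfluous.

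**Conclusion.** The point holds as a minor improvement to the schedule. Admissions are the only safety measure in Table 4 without a baseline, although the same source is used at baseline for outpatient contacts. No covariate named in the article takes the place of prior admissions. The admissions comparison remains valid, but is less precise than it need be.

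The gain cannot be fixed from the article. The illustrative 9 % to 25 % of variance rests on an assumed correlation of 0.3 to 0.5 and on a linear model; a weaker correlation would make it smaller.

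The deaths tick and the source label are clerical. Sample size, type I error, and the primary and secondary outcomes are unaffected.

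**What to change.** - Remove the baseline tick for deaths in Table 4.
- Add a baseline for number of admissions and bed-days, psychiatric and somatic, over a fixed period before randomisation. Eighteen months would mirror the main follow-up, but any fixed length serves if it is stated in advance.
- State that the admissions analysis adjusts for this baseline alongside the stratification variables, with a model suited to skewed counts, for example negative binomial regression. A simple rank test could not carry the covariate.
- State one source for admissions and outpatient use at baseline, 18, 30 and 60 months, so that the hospital-records label agrees with the register heading of the last column and with the abstract.

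The cost is a table correction, a longer extraction window for hospital data and slightly more analysis work. No participant contact is added.
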